### Plans to promote participant retention and complete follow-up {18b}

Study follow-up visits will coincide with participants’ routine visits to the health clinics. Pregnant women in *Nyagatare* District are encouraged to visit health centers every month during their pregnancy. The *Deux Oeufs* study will conduct visits for the trial during two of these scheduled visits at approximately 20–26 weeks and 30–34 weeks of gestation. Participants will also receive a text and phone reminder prior to each visit. The women also visit health clinics at approximately 6 weeks and 6 months after birth for infant vaccination and a well-child exam. The study team will schedule study visits with these routine appointments. Transportation to and from these visits is provided by the study, thus increasing not only retention in the study but also routine ANC and well-child health visits.

### Data management {19}

All data, except biological samples and ultrasound images, will be collected on encrypted tablets using the Research Electronic Data Capture (REDCap). Daily compliance data of the intervention will be collected using encrypted smartphones using REDCap. GPS location of participants’ houses without identifiable data will be collected using a handheld GPS device (Garmin 65). Regular monitoring will ensure data quality. Range checks for the data values will be automated to identify human errors while filling out the forms. All data will be transferred to a central server on a weekly basis and will be processed and analyzed with R and Stata.

### Confidentiality {27}

All data will be collected on encrypted tablets. Data marked as identifiable will be restricted to the principal investigators (PIs) and only those staff requiring access for logistics and quality control purposes. Access to the de-identified data will be granted to a statistical team for interim statistical analyses through a secure institutional portal. De-identified ultrasound images may be shared with an evaluator for quality control. The evaluator will not have access to identifiable information.

Biological samples and ultrasound images will only be marked with the participant identification number and will not have identifiable data attached to them.

Data will be de-identified and stored for future use after the completion of the study. The de-identified data set will not include any information that could lead to the identification of study participants, following the guidelines established by the HIPAA. Identifiable data will be destroyed after completion of the study. Long-term preservation of the de-identified data will ensure accessibility beyond the project’s life. After the completion of the project, the de-identified data will be deposited into the Data Repository of the University of Florida and the USAID data repository, where it can be publicly accessed. The dataset in the USAID repository will be findable and identifiable through a study digital object identifier (DOI).

### Plans for collection, laboratory evaluation, and storage of biological specimens for genetic or molecular analysis in this trial/future use {33}

As described above, maternal blood samples will be drawn at enrollment, second trimester, third trimester, and 6-week and 6-month visits. A total of 12-ml blood will be drawn from women and will be stored in three tubes (4 ml each). Maternal hemoglobin concentrations will be measured at the point of care using a Sysmex poch-100i automated hematology analyzer. Infant blood samples will be drawn at 6 weeks and 6 months of age. Drawn blood from the mother and infant will be kept in a cooler box with ice packs and, after isolating the serum, will be put into a −20 °C cooler within 8 h of collection. Within 7 days of collection, the sample will be transferred to Kigali for longer-term storage in −80 °C freezers at the University of Rwanda or Rwanda Biomedical Center. From the blood samples collected, a lipid (LDL and HDL cholesterol, triglycerides, HDLC4) and glucose panel will be measured among women at first, second, and third trimester visits and post-birth visits at 6 weeks and 6 months. These tests will be done at the *Nyagatare* district hospital using a *Roche Cobas c311* chemical analyzer.

The present study has approval for blood draws and long-term storage, but plans for further analyses are pending additional funding. Examples include the following:Maternal serum biomarkers of nutritional status and inflammation at third trimester and at 6-week and 6-month postpartum. These may include but are not limited to soluble transferrin receptor (sTfR), ferritin, retinol-binding protein (RBP), C-reactive protein (CRP), and alpha-1-acid glycoprotein (AGP).Child serum biomarkers of nutritional status and inflammation at birth and 6-week and 6-month postpartum. Pending funding, these may include but are not limited to sTfR, ferritin, RBP, CRP, and AGP.

Hair samples will be collected from women to assess cortisol levels, a hormone indicative of stress. Hair samples will be stored in zipped plastic bags at room temperature until transport for laboratory analysis.

## Statistical methods

### Statistical methods for primary and secondary outcomes {20a}

The primary analysis of the RCT will be based on a modified intention-to-treat (ITT) principle. This trial is designed to formally test the mean difference in the primary outcome of birth LAZ between the treatment arm and the control arm (T1–T2). All women who have a live birth and for whom childbirth length is measured within 72 h will be included in the analysis of the primary outcome. Cases for whom primary outcome data are not available (missing) will not be included in analyses. Descriptive analysis, such as frequency and percentages, will be reported for categorical variables, while means, standard deviation, and quartiles will be reported for continuous variables.

For secondary outcomes, the two-sample *t*-test will be used if the outcome is normally distributed with or without transformation, and the Wilcoxon rank-sum test will be used if the outcome is not normally distributed, where normality will be assessed using the Shapiro–Wilk test and Q-Q plot. Kruskal–Wallis and two-sample rank sum tests will be used if their distribution is non-normal. For both primary and secondary outcomes at birth, exploratory analyses will be conducted using multivariable linear or logistic regression models to adjust for potential confounders (such as baseline SES, gestational age at birth, mother’s education, mother’s age, and dietary diversity) that may be imbalanced across treatment arms. Imbalance of baseline factors may occur as a post-randomization selection bias or by chance alone. Post-randomization selection bias is possible, especially given that participants are not blinded. If this occurs, it will be crucial to adjust for imbalanced confounders in all regression analyses. Village-level heterogeneity will be considered using random effects. Spatial correlation in village-level random effects will be adjusted for if spatial clustering patterns in the outcomes are present. For longitudinal outcomes such as head circumference, linear or generalized linear mixed models will be used to account for heterogeneity in the intercept and slope of growth.

All statistical analyses will be conducted using R and Stata. The statistical significance for regression models will be set at *p* < 0.05 without further adjustment for multiple comparisons.

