## Trial design {8}

The study is a randomized controlled trial (RCT) with parallel 1:1 assignment of participants to two study arms: (T1) two eggs per day (intervention) or (T2) typical diet (control). Block randomization will be stratified by gestational age group (09 < 11 weeks and 12 < 14 weeks). Women in the intervention arm will be asked to consume two eggs per day under the direct observation of study staff at a community health worker (CHW) home. Participants in the control arm will be asked to consume their typical diet, including CSB+. All participants will continue to receive standard care for pregnant women (antenatal care and institutionalized births among others), as outlined by the GoR. In addition, the study will provide a mobile phone, family health insurance (if not already covered), and modest compensation for participation. The amount of compensation was determined based on formative research and approved by the Rwandan National Ethics Committee (RNEC). The compensation for each engagement at the clinic (first, second, and third trimester visits, birth and two postpartum visits, at 6 weeks and 6 months of child age) was decided to be 3000 RWF. They will also be provided with transportation reimbursement for the study visits that occur at the health centers. All participants not receiving Shisha Kibondo (government brand for CSB++) from the GoR as part of their standard prenatal care will receive the same amount (6 kg/month) from the study. Figure 1 illustrates the study recruitment flow and treatment allocation.

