### Sample size {14}

Nutritional interventions during pregnancy have yielded mixed results in their impact on LAZ at birth. Previously reported mean difference in LAZ ranges from 0.12 [2, 18] to 0.29 [12, 17]. Notably, the 0.29 effect size observed by Dhaded et al. [12] was associated with nutritional supplementation initiated prior to conception, whereas supplementation beginning in the first trimester yielded a smaller effect size of 0.21. Considering most studies report an effect size below 0.20 and based on the available literature on other food supplementation as found in some literature review papers by Imdad and Bhutta [23] and Stevens et al. [46], we hypothesize a mean difference of 0.18 in LAZ to be both a reasonable and clinically meaningful effect size. As such, we calculate the sample size based on testing two hypotheses simultaneously:$$H0:d1\leq0\;vs.\;Ha:d1>0$$

For our hypothesized effect size, the sample size required with 20% attrition (accounting for pregnancy loss, stillbirths, and loss of follow-up) to attain an 80% marginal power with a 5% level of significance was 478 per arm, based on a two sample one-sided test. Thus, we aim to enroll an overall sample of 956 women in the proposed study. Sample calculation was performed using “pwr” package [5] in RStudio.

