### Sequence generation {16a}

The study will apply stratified block randomization with varying block sizes to randomly assign the treatment arms and to preserve the balance of treatment across gestational age groups (9–11 weeks and 12 < 14 weeks). A chain of blocks will be pre-generated for each stratum, e.g., 1000 blocks. The size of each block will also be randomly and independently chosen as 2, 4, or 6 individuals. The study will use the tool at sealedenvelope.com to generate the randomization list. The random seed will be generated using the random integer generator at random.org, which introduces randomness from unpredictable atmospheric noise (see more below).

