## Data collection and management

### Plans for assessment and collection of outcomes {18a}

At enrollment, an ultrasound screening will be conducted to determine eligibility, followed by a baseline survey on demographic and background characteristics of the household. Questions in the survey will include pregnancy and medical history, maternal behavior towards risk factors (e.g., malaria), physical activity, dietary diversity using the Dietary Quality Questionnaire (DQQ) (Global Diet Quality Project), household food security using the Household Food Insecurity Access Scale (HFIAS) [8], and water and sanitation practices. Women’s anthropometric measurements will be taken using Seca scales, including height (Seca 213 portable measuring rod), weight (Seca 874), and mid-upper arm circumference (MUAC). Blood samples and hair samples will also be collected at baseline.

During two additional clinical visits in the second (20–26 weeks) and third trimester (30–34 weeks), anthropometric measurements (height, weight, MUAC) from all women will be taken, as well as blood and hair samples. Ultrasound measurements will also be taken to assess fetal growth measures that include biparietal diameter, head circumference, abdominal circumference, and femur length. Information on medical conditions since the last visit, depression screening using the Edinburgh Postnatal Depression Scale (EPDS), physical activity, breastfeeding intention, consumption and preparation recall of CSB+, and maternal diet (DQQ) will be collected using a short survey during these visits.

At birth, anthropometric measurements of all neonates will be assessed twice within 72 h after birth, with the first 24 h as the target window. A third measurement will be taken in case of discrepancies between the first two measurements. For recumbent length, a third measurement will be taken if the difference between the first two measurements is more than 0.7 cm. A third weight measurement will be taken in case the difference in the weight in the first two measurements is more than 10 g. Length measurements will be taken using length board S0114540 set3, and weight will be measured using Seca 334 scale.

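### The confirmatory birth LAZ comparison leaves out the randomisation stratum and baseline predictors already collected; it is valid but gives up precision, and the adjusted models are exploratory, imbalance-driven and include a post-randomisation covariate

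*Protocol article*

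**What the plan says.** **Primary outcome.** Statistical methods {20a} states that the trial is designed to "formally test the mean difference in the primary outcome of birth LAZ between the treatment arm and the control arm". It names no model, stratum or covariate for this comparison. Sample size {14} derives the target for a difference of 0.18: the number required "to attain an 80% marginal power with a 5% level of significance was 478 per arm, based on a two sample one-sided test".

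**Adjustment.** Section {20a} describes multivariable linear or logistic models, for primary and secondary outcomes at birth, as exploratory. The covariates are introduced as examples of confounders that might be imbalanced: baseline SES, gestational age at birth, mother's education, mother's age and dietary diversity. Adjustment is called crucial if imbalance arises through post-randomisation selection. The stratum is not listed.

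**Randomisation.** Trial design {8} says allocation is "stratified by gestational age group (09 < 11 weeks and 12 < 14 weeks"). Sequence generation {16a} says blocks will "preserve the balance of treatment across gestational age groups", and gives the groups as 9–11 weeks and 12 to under 14 weeks.

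**Baseline data.** Section {18a} records at enrolment "height (Seca 213 portable measuring rod), weight (Seca 874), and mid-upper arm circumference (MUAC"). Table 2 adds medical, obstetric and pregnancy history.

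**Secondary outcomes.** A t-test is used if the outcome is normal, with or without transformation; "the Wilcoxon rank-sum test will be used if the outcome is not normally distributed". Normality is judged by the Shapiro–Wilk test and a Q-Q plot.

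**The concern.** Randomisation is stratified by gestational age at enrolment, yet the stratum appears in no analysis. Maternal size and obstetric history are collected at enrolment and could predict birth length, yet they have no place in the confirmatory comparison. Where adjustment is described, three features weaken it:

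- It depends on imbalance seen in the data, so the model is not fixed in advance.
- The covariates are examples, not a list.
- Gestational age at birth could be affected by the eggs, and preterm birth is itself a secondary outcome in Table 1. Conditioning on it may remove part of the effect or distort it.

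What is at stake is precision and prespecification. The Trial status section says enrolment is paused for lack of funding, so 956 may not be reached. Adjustment for baseline data recovers some precision without recruiting anyone.

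A lesser point concerns continuous secondary outcomes. The data decide between a difference in means and a rank comparison, so the quantity estimated can differ from outcome to outcome and is unknown until the data are seen.

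The stratum boundaries also disagree between two sections. This must be settled before the stratum can enter a model.

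**Working it through.** **Inputs from the document:** difference 0.18, one-sided α 0.05, power 80%, 20% attrition, 1:1 allocation, 478 per arm.

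**Assumptions:** SD of LAZ = 1 (not stated; implied because 0.18 is also called an effect size and SD 1 reproduces the target). R², the share of LAZ variance explained by stratum and baseline covariates, is not stated, so a range is shown.

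**Step 1: reproduce the plan's figure.**

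n = 2(1.645 + 0.842)² / 0.18² = 381.6, so 382 evaluable per arm.

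382 / 0.8 = 477.5, so 478 per arm and 956 in total. This matches exactly. A two-sided version needs 485 evaluable, 607 enrolled per arm, and does not match. The target therefore belongs to an unadjusted, one-sided comparison with no covariate gain built in.

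**Step 2: power after adjustment.** The residual SD is √(1 − R²). With SE = √(2/382) = 0.07236 when R² = 0,

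power = Φ(0.18 / [0.07236·√(1 − R²)] − 1.645).

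The equivalent evaluable number is 382/(1 − R²).

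| Assumed R² | One-sided power | Equivalent evaluable per arm | Enrolled per arm for 80% power |
|---|---|---|---|
| 0 | 80.0% | 382 | 478 |
| 0.01 | 80.4% | 386 | 473 |
| 0.02 | 80.7% | 390 | 469 |
| 0.05 | 81.8% | 402 | 454 |
| 0.10 | 83.6% | 424 | 430 |
| 0.20 | 87.2% | 478 | 383 |

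**Step 3: the stratum alone.** If a factor balanced by design is left out, the unadjusted SE is too large by a factor 1/√(1 − R²). The true one-sided α is then 1 − Φ(1.645/√(1 − R²)): 0.0492 at R² = 0.01 and 0.0457 at R² = 0.05. The test errs on the conservative side. At R² = 0.01 the unadjusted test has 80.2% power and the stratum-adjusted test 80.4%. The stratum has two levels within 9 to under 14 weeks, and LAZ is already standardised by INTERGROWTH, so a low R² for the stratum is plausible.

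**Step 4: is a normality check needed?** In simulation with exponential data (skewness 2) and 382 per arm, the two-sided type I error of the t-test was about 5%. At this size, comparing means does not depend on passing a normality test.

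**Step 5: stratum definitions side by side.** Eligibility runs from 9 weeks to 13 weeks + 6 days. Read literally, Trial design {8} covers 9+0 to 10+6 and 12+0 to 13+6, so 11+0 to 11+6 falls in neither group. Sequence generation {16a} has 9–11 weeks, which in completed weeks includes 11+0 to 11+6.

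**The case against.** **The primary test is not named.** Section {20a} gives no test for LAZ; the two-sample test appears only in the sample size section. Village random effects are to be considered, and the text does not clearly confine them to the exploratory models. Covariate lists are often left to the SAP. This stands in part: unadjusted is a reading of two sections together. But the protocol does not stay silent on adjustment. It labels it exploratory, and a SAP could not make it primary without departing from that.

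**An unadjusted difference in means is an accepted analysis.** This stands. A reader might infer that the test is invalid or the sample size wrong. Neither follows: the omitted stratum makes the test at most slightly conservative, and 478 reproduces exactly. Nor do the documents support starting from 70% power. That is the two-sided figure, while the plan is one-sided at 80%.

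**The gain is assumed.** This also stands. At R² of 0.02 to 0.05, power reaches only 80.7% to 81.8%.

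**The normality check does not clearly cost precision.** A reader might infer that it does. For gamma data the rank test's asymptotic efficiency relative to the t-test is 0.97 at skewness 0.3, 1.02 at 0.6 and 1.17 at 1.0, so the loss is trivial or reversed. Shapiro–Wilk alone rejects skewness of 0.3 in about 56% of samples of 382, but the plan also uses a Q-Q plot and allows transformation, so that is not the planned procedure's rejection rate. Table 1's means and SDs are descriptive and do not promise a mean difference. Longitudinal outcomes go to mixed models, which narrows the check's reach. What remains is that test and estimand depend on the data.

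**Other wording.** Mentioning Kruskal–Wallis with two arms is harmless, and the main test for binary outcomes can be left to the SAP.

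**Conclusion.** The point holds as a matter of efficiency and prespecification. Sections {14} and {20a} together make the confirmatory LAZ comparison unadjusted. Adjustment is exploratory, driven by imbalance, and includes a post-randomisation variable among its examples. Nothing here invalidates the primary test or the sample size.

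For assumed R² of 0.05 to 0.20, SD 1 and 382 evaluable per arm, the precision forgone is worth about 2 to 7 percentage points of one-sided power, or 5% to 25% more evaluable women (402/382 to 478/382). Almost all of it would come from baseline predictors, not the stratum. The documents give no R², so the true gain could be smaller.

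The data-driven choice of secondary tests is a real but lesser weakness, because the estimand is not fixed. The mismatch in stratum definitions is a plain inconsistency. The change is worth making but is not essential to validity.

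**What to change.** - **Primary analysis:** a linear regression of birth LAZ on arm, gestational-age stratum and a short list of baseline covariates fixed in advance, for example maternal height, BMI or MUAC, age and obstetric history. Report the adjusted difference with a confidence interval. Leave out gestational age at birth and any other post-randomisation variable. Do not make adjustment depend on observed imbalance.
- **Sensitivity analysis:** the unadjusted difference in means.
- **Continuous secondary outcomes:** the same model form, replacing the normality-based choice between t-test and Wilcoxon. Keep mixed models for longitudinal outcomes.
- **Strata:** state one definition in both Trial design {8} and Sequence generation {16a}, matching the randomisation lists actually used and covering the whole eligible range, including 11+0 to 11+6 weeks.

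The cost is a wording amendment, best made before unblinded primary outcome data are seen. The baseline variables are already collected, and neither the sample size nor trial conduct changes.

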	Small vulnerable newborn status	Binary	Any of: SGA (< 10th), preterm (< 37 weeks), or low birthweight (< 2500 g)	Within 72 h of birth	Proportion
	Head circumference z-score	Continuous (z-score)	INTERGROWTH 21st growth standards	Within 72 h of birth	Mean (SD)
* Infant measurements*	Prevalence of stunting among infants	Binary	Length-for-age < −2 SD according to the WHO Multicenter Growth Reference Study standards	At 6 weeks and 6 months of age	Percentage
	Infant weight-for-age z score	Continuous (z-score)	WHO Child Growth Standards	At 6 weeks and 6 months of age	Mean (SD)
	Prevalence of underweight	Binary	Weight-for-age < -2 SD according to the WHO Multicenter Growth Reference Study standards	At 6 weeks and 6 months of age	Percentage
	Child neurodevelopment- HNNE	Continuous/domain score	Hammersmith Neonatal Neurological Examination (HNNE)	At 6 weeks of age	Domain and total scores
	Child neurodevelopment-CREDI	Continuous	Caregiver-Reported Early Childhood Development Instrument (CREDI) score (long form)	At 6 months of age	Domain-specific scores

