*** Maternal outcomes***					
	Maternal weight	Continuous (in kg)	Measured using calibrated scale	At enrollment (between 9–< 14-weeks gestation), 20–26-weeks gestation, 30–34-weeks gestation, and during labor/delivery	Mean (SD)
	Maternal weight gain	Categorical (inadequate/adequate/excessive)	IOM guidelines and calculated based on maternal weight at labor/delivery-maternal weight at enrollment	At enrollment (between 9–< 14 weeks gestation), 20–26-weeks gestation, 30–34-weeks gestation, and during labor/delivery	Proportions
	Maternal prenatal and postnatal depression	Continuous and binary	Edinburgh Postnatal Depression Scale (EPDS) (range 0–30; 12 or higher defining maternal depression)	At 6 weeks and 6 months of child age	Mean (SD), prevalence above threshold
	Maternal cortisol concentration	Continuous	Cortisol concentration from maternal hair samples	Between 9–< 14 weeks, 20–26 weeks, and 30–34 weeks gestational ages, at time of birth, and at 6 weeks and 6-months post birth	Mean (SD)
	Minimum Dietary Diversity for Women (MDD-W)	Binary	Diet Quality Questionnaire (DQQ) will be used to generate MDD-W, used here as meeting the validated threshold or not 0–10 scale, where a higher score indicates more diversity (better) with threshold of having at least 5 to have met minimum requirements (coded as 0 for not having met/1 for having met MDD)	Between 9–< 14 weeks, 20–26 weeks, and 30–34 weeks of gestational ages, at time of birth, and at 6-week and 6-month post-birth	Proportion
	Dietary diversity score	Continuous	Sum of score from different food groups 0–10	Between 9– < 14 weeks, 20–26 weeks, and 30–34 weeks of gestational ages, at time of birth, and at 6-week and 6-month post-birth	Mean DDS
	Maternal hemoglobin	Continuous/categorical	Trimester-specific WHO cutoffs	Between 9– < 14 weeks, 20–26 weeks, and 30–34 weeks of gestational ages, at time of birth, and at 6-week and 6-month post-birth	Mean (SD), anemia prevalence by trimester
	Biomarkers of micronutrient status, growth factors, systemic inflammation, environmental enteric dysfunction, metabolomics, choline, and lipid panel (including HDL and LDL cholesterol)	Continuous	Measured using whole blood or serum samples among women and infants	Between 9– < 14 weeks, 20–26 weeks, and 30–34 weeks of gestational ages, at time of birth, and at 6-week and 6-month post-birth	Mean (SD)

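### The t-test/rank-test rule is worded for all secondary outcomes but does not suit the binary ones or the three-class weight-gain outcome

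*Protocol article*

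**What the plan says.** The second paragraph of the Protocol's section {20a} opens with secondary outcomes in general. A t-test comparing the two arms "will be used if the outcome is normally distributed with or without transformation". Failing that, the rule turns to ranks, and its words are that the "Wilcoxon rank-sum test will be used if the outcome is not normally distributed". Normality is judged by the Shapiro–Wilk test and a Q-Q plot. A further sentence repeats the rank branch: "Kruskal–Wallis and two-sample rank sum tests will be used if their distribution is non-normal". Nothing limits the rule to continuous outcomes.

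Two other kinds of model follow. The first has the scope "For both primary and secondary outcomes at birth". The plan says of it that "exploratory analyses will be conducted using multivariable linear or logistic regression models"; these adjust for possible confounders, with gestational age at birth among the examples. The second is for longitudinal outcomes, with head circumference as the example, where "linear or generalized linear mixed models will be used to account for heterogeneity in the intercept and slope of growth". The preceding paragraph promises frequencies and percentages for categorical variables.

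Table 1 lists these secondary outcomes that are not continuous:

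- **At birth, binary:** SGA at two cut-offs, preterm live birth, low birthweight, and small vulnerable newborn, defined as "Any of: SGA (< 10th), preterm (< 37 weeks), or low birthweight (< 2500 g").
- **At 6 weeks and 6 months, binary:** stunting, underweight, and maternal depression by EPDS threshold (EPDS is also scored continuously).
- **At repeated visits, binary:** minimum dietary diversity (MDD-W).
- **Three classes:** maternal weight gain, "Categorical (inadequate/adequate/excessive"), summarised as proportions.

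**The concern.** None of these binary or three-class outcomes can be normally distributed, so the rule as worded sends them all to a rank test. That raises two separate problems.

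For a binary outcome, the rank test returns a p-value and no useful effect measure. The birth-outcome question in section {7} asks whether eggs improve outcomes such as preterm birth, low birthweight and SGA. A reader will want the size of the difference with a confidence interval, from an analysis that is not labelled exploratory.

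For weight gain, a rank test needs an order. The obvious one is inadequate, adequate, excessive, which puts the desirable class in the middle. Moves into adequate from the two ends then cancel, and a move from adequate to excessive counts as a rise. Weight gain is named in the first maternal research question, so a misleading answer there would matter.

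**Working it through.** **Number per arm.** Section {14} gives a LAZ difference of 0.18, one-sided 5%, 80% power and 20% attrition. SD 1 is assumed because the outcome is a z-score. Then n = 2 × (1.645 + 0.842)² / 0.18² ≈ 382 per arm, and 382 / 0.8 = 477.5, rounded up to 478. The stated 478 reproduces. It has no bearing on the point beyond supplying 382 as a realistic number analysed per arm.

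**Binary outcome.** Assumed risks are about 20% in control (76/382) and 14% in the egg arm (53/382).

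- Rank-sum p = 0.0264; Pearson chi-square p = 0.0263. As a test, the rank-sum is sound.
- The Hodges–Lehmann shift that goes with the rank test is 0, which tells the reader nothing.
- Risk difference = 53/382 − 76/382 = −6.0 points. Its SE is √(0.199 × 0.801/382 + 0.139 × 0.861/382) = 0.027, so the 95% CI is −11.3 to −0.7 points.
- Risk ratio = 53/76 = 0.70. Odds ratio = (53/329)/(76/306) = 0.65.

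**Weight gain.** The Protocol gives no class shares, so every share below is an assumption, written inadequate/adequate/excessive. With classes ordered that way, the rank-sum test assesses θ = P(egg > control) + ½P(tie), with null value 0.5. Power is from simulated trials with 382 per arm at two-sided 5%.

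| Control → egg arm (%) | θ | Rank-sum significant | Inadequate vs not | Excessive vs not |
|---|---|---|---|---|
| 40/35/25 → 30/55/15 (better at both ends) | 0.5075 | about 7% | about 82% | about 94% |
| 50/35/15 → 50/20/30 (only more excessive) | 0.5375 | about 50%, as higher | no change | over 99% |
| 60/30/10 → 60/20/20 (only more excessive) | 0.520 | about 20%, as higher | no change | about 97% |
| 60/35/5 → 50/43/7 (excessive uncommon) | 0.5515 | about 81% | about 80% | about 21% |

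In the first row θ = 0.30 × 0.20 + 0.55 × (0.40 + 0.175) + 0.15 × (0.75 + 0.125) = 0.060 + 0.316 + 0.131 = 0.5075. Ten points leave each tail and the two moves nearly cancel. In the second row θ = 0.50 × 0.25 + 0.20 × 0.675 + 0.30 × 0.925 = 0.5375, so a purely adverse shift reads as an increase.

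A single data set at the third row's shares gives rank-sum p = 0.29 and 3 × 2 chi-square p = 0.00003. In the fourth row nothing is lost.

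**Do the other named models fill the gap?** Logistic regression is confined to outcomes at birth and labelled exploratory. If gestational age at birth is used as a covariate, it wholly determines preterm birth, which Table 1 defines as delivery before 37 + 0 weeks. It is also a post-randomisation variable for low birthweight and small vulnerable newborn. Generalized linear mixed models could carry stunting, underweight, depression and MDD-W, but the text ties them to growth trajectories and does not assign those outcomes to them. Neither model is assigned to the three weight-gain classes.

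**The case against.** The strongest reply is that the rule was meant for continuous outcomes. A normality check with optional transformation makes sense only there, the preceding paragraph treats categorical variables separately, and Table 1 summarises weight gain as proportions. On that reading the article merely omits the categorical tests. A condensed article may leave those to an analysis plan that is not shown. The reply is plausible as to intent, but the sentence says otherwise: it covers secondary outcomes without restriction, and an analysis plan written to it would carry the mismatch forward.

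Several stronger readings are tempting and not supported:

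- *That t-tests and rank tests are the only methods stated.* Logistic regression and generalized linear mixed models are named as well.
- *That the plan ranks excessive above adequate.* No order is stated; the ranking follows only from applying the rule literally. Class percentages by arm will be reported, so a shift into excessive gain would be visible.
- *That the analysis of binary outcomes is invalid or leaves effects unknowable.* The rank-sum p-value practically equals the chi-square p-value, and a crude risk difference follows from the reported proportions. What is missing is a planned estimate with a confidence interval.
- *That odds ratios are wrong.* They are a legitimate measure, and preferring risk ratios is a choice of presentation.
- *That the 7% and 50% figures are expected losses.* They come from adverse assumed shares; the last row of the table shows no loss.

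**Conclusion.** The point holds as a mismatch between a stated rule and the outcomes it is said to cover. For binary secondary outcomes the consequence is modest: a valid p-value without a planned, non-exploratory effect estimate at birth, and no explicit model assignment later on. For weight gain it could be misleading, but only if the rule is applied literally with the natural class order. Its size then runs from nothing to almost complete loss of power or a wrong-direction signal, depending on shares that the document does not give. The primary outcome and the sample size are unaffected. Severity is minor to moderate.

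**What to change.** In section {20a}:

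1. Limit the t-test/rank-test rule to continuous secondary outcomes.
2. State that binary secondary outcomes are analysed by risk difference and/or risk ratio with a 95% CI, adjusted for the gestational-age randomisation stratum. Stratified Mantel–Haenszel, or a binomial or Poisson model with robust errors, would serve. For outcomes at repeated visits, say whether the mixed model or this analysis applies.
3. Compare maternal weight gain as two proportions: inadequate versus not, and excessive versus not.

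The cost is wording in the protocol or analysis plan and one extra contrast for weight gain. No new data are needed.
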